**TABLE 1: SCHEDULE OF STUDY PROCEDURES (CASE SUBJECTS ONLY)**

| Study Phase                                | Screening/Initial Assessment |          | Treatment/Intervention |          |
|--------------------------------------------|------------------------------|----------|------------------------|----------|
|                                            | 1                            | 2        | 3                      | 4        |
| Visit Number                        | 1                     | 2 | 3               | 4 |
| Study Days                          |                              |          |                        |          |
| Informed Consent/Assent                    | X                            |          |                        |          |
| Review Inclusion/Exclusion Criteria        | X                            |          |                        |          |
| Medical Record Review                      | X                            |          | X                      | X        |
| Optometric Examination                     | X                            |          | X                      | X        |
| CISS-Con and VisQual-T                     | X                            |          | X                      | X        |
| VRS3                                       | X                            |          | X                      | X        |
| VET                                        | X                            |          | X                      | X        |
| fMRI (NJIT Clinical site only)             |                              | X        | X                      | X*       |
| Pregnancy test** (NJIT Clinical site only) |                              | X        | X                      | X        |
| Randomization                              |                              | X        |                        |          |
| Adverse Event Assessment                   |                              |          |                        |          |

\*=Arm 2 only

\*\*=Female subjects only

**FIGURE 1: STUDY DIAGRAM (CASE SUBJECTS ONLY)**

[figure not shown]

## **1 BACKGROUND INFORMATION AND RATIONALE**

### **1.1 Introduction**

Typically occurring convergence insufficiency (TYP-CI) is the most common binocular vision disorder in children and young adults. As such, recent literature has focused on the neural-mechanistic basis of, and treatment for, TYP-CI. These recent studies have been effective in remediating symptoms and improving vision in both children and adults using office-based vergence/accommodative therapy (OBVAT). However, these studies have not had participants with a history of head injury. The prevalence of convergence insufficiency (CI) in child and adults with persistent post-concussive symptoms (PPCS-CI) is higher than in the non-concussed populations, however there is no validated treatment for PPCS-CI

While the use of OBVAT in TYP-CI has been shown to be effective, its use in PPCS-CI has not been examined. This randomized controlled trial seeks to determine if OBVAT in addition to standard-community concussion care (SCC) improves recovery among adolescents and young adults with PPCS-CI (11 to 35 years of age).

### **1.2 Name and Description of Investigational Product or Intervention**

This study involves an OBVAT intervention to determine if SCC + OBVAT improves convergence insufficiency for adolescents and young adults after concussion.

### **1.3 Relevant Literature and Data**

Adolescent and young adult concussion is now considered a substantial health problem in the United States. According to studies from BlueCross BlueShield between 2010 through 2015, the prevalence of concussion diagnosis has increased by 71% in the 10 to 19 year old age group. While some symptoms resolve with supportive care, a longitudinal study showed that 41% of the 591 concussed patients studied were classified as having persistent post-concussion symptoms (PPCS) where symptoms did not dissipate after two weeks. Another study reported that 46% of the 2946 enrolled children had a diagnosis of PPCS two-weeks post-injury which decreased to 33% four weeks post-injury.

This study is important because PPCS has a profound impact on a person's ability to function scholastically and professionally. Adolescents are particularly vulnerable to the cognitive and developmental concussion consequences, often having a prolonged recovery and poorer outcomes than adults. Oculomotor dysfunction is so common in PPCS that it is considered one of the phenotypes of concussion, owing to its frequent occurrence. Symptoms include dizziness, headaches, inability to sustain attention during a long duration task, fatiguing faster post-injury compared to pre-injury, difficulty with attention and memory, and blurry /double vision. Convergence insufficiency (CI), is associated with many of the aforementioned characteristic symptoms. In one study of PPCS, 70.4% of 260 concussed athletes report visual disturbances, which was the 7th most frequently reported symptom.

---

CI is the most common non-strabismic binocular vision disorder in children and young adults, with prevalence estimates from school-based populations ranging from 3.4% to 12.7% for typically-occurring CI (TYP-CI) that is not associated with concussion. Much higher rates of CI have been reported in children and young adults with PPCS-CI, with estimates of 38% to 49% for children and 44% to 47% for adults. Since PPCS-CI is associated with a traumatic acceleration of the head resulting in injury, this suggests a different etiology than TYP-CI, which presumably develops over time and is not associated with head injury. In addition, vestibular dysfunction is commonly associated with PPCS-CI, which is not the case for TYP-CI. While both conditions share some similar clinical characteristics (receded near point of convergence, inadequate positive fusional vergence), the higher prevalence, sudden onset, and frequent comorbidity of vestibular dysfunction combined with our pilot data suggest that PPCS-CI may be a unique physiological condition compared to TYP-CI. Objective eye movement recording with novel eye movement stimulus protocols to understand the underlying neural substrates assessed using functional MRI (fMRI) is needed. These measures will delineate the differences between the two CI subtypes since conventional and often subjective clinical measurements are not substantially different. With this knowledge, physicians will be positioned to develop more effective diagnostic and therapeutic strategies for the treatment of PPCS-CI, that can lead to faster return to school, sports, or work.

For TYP-CI, diagnostic protocols and therapeutic interventions are well-established and results from multiple randomized clinical trials (RCT) summarized in a systematic Cochrane Review show that office-based vergence and accommodative therapy (OBVAT) is an effective treatment in TYP-CI children and young adults, In fact, the PI along with Drs. [name], [name], and [name] are the only group to use objective eye movement recording with fMRI to show the underlying neural mechanistic differences between TYP-CI and binocularly normal controls (BNC) as well as the neural mechanism of how OBVAT changes the neurophysiology and visual function in TYP-CI. Our group and others have published pilot studies studying only a single treatment arm and suggest that the same 12 one-hour sessions of OBVAT that is effective for TYP-CI may improve visual function for PPCS-CI. Yet, a properly powered randomized clinical trial investigating the effectiveness of OBVAT for PPCS-CI is not available, nor are studies that compare different doses, or provide an understanding of the neural mechanism by which therapeutic interventions may be remediating symptoms and improving vergence function.

Office-Based Vergence and Accommodative Therapy (OBVAT) studied in many prior RCT has four phases. The first phase will be designed to manage some of the visual/vestibular issues common in PPCS-CI using eye movements associated with head and body movement. In phase 2, techniques will be used to stimulate gross convergence, positive fusional vergence and monocular accommodative therapy using Brock string, Vectograms, Computer Orthoptics and Lens Accommodative Rock, respectively. Once the subject can perform these tasks with ease, s/he will graduate to the third phase which is ramp fusional vergence and monocular accommodative therapy with Vectograms, Aperture Rule, Lifesaver Cards and Lens Accommodative Rock. The final stage will consist of jump fusional vergence and binocular accommodative facility. The goal of the initial phase is to remediate vestibular issues if present. If there are no vestibular issues, then this phase will be omitted.

Home reinforcement will be used to augment subjects' progress in OBVAT. The home

---

reinforcement software stimulates disparity convergence, and sequences the therapy from ramp to step vergence demands, always providing immediate and accurate feedback to the patient which has been shown to improve vision function. The software also allows the investigator to monitor compliance and performance with the prescribed treatment by logging the number and time of sessions.

Standard-Community Concussion Care (SCC) consists of physical and cognitive rest immediately following the injury for a brief period of time to allow symptoms to abate, followed by a gradual reintroduction of academic and physical activities, restricting activities at high risk for repeat brain injury (such as contact or collision sports) until a graded return to play protocol has been completed without provoking symptoms. For those patients who still have vestibular signs and symptoms persisting beyond 1-month post injury, initiation of vestibular and balance rehabilitation (VBT) physical therapy may occur, as determined by the physician with the goal of improving motion tolerance and balance through exercises that include adaption by retraining the vestibular ocular reflex. While some physical therapists incorporate pencil pushups or Brock string (common treatments for CI) into their VBT protocols, they will be instructed specifically not to include any convergence exercises targeting CI.

This study will incorporate two objective eye movement experiments with corresponding fMRI experiments: VRS3 and VET. The VRS3 and VET will be used to determine the physiological similarities or differences between TYP-CI and PPCS-CI, while the corresponding fMRI experiments will reveal the brain-behavior relationship.

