### **3.2 Allocation to Treatment Groups and Blinding**

A member of the study team will randomize case subjects who consent to participate into one of the treatment groups at the conclusion of their initial assessment using a random number generator. Optometrists will be blinded to the treatment group.

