### **3.4 Study Population**

#### **3.4.1 Inclusion Criteria (examples)**

#### **3.4.2 Index/Case Subject Inclusion Criteria**

- 1) Males or females age 11 to 35 years.
- 2) Best-corrected visual acuity of 20/25 in both eyes at distance and near.
- 3) Willingness to wear glasses or contacts to correct refractive error, if needed.
- 4) Global stereopsis of 500 sec of arc or better using Randot Stereo Test and local stereopsis of 70 sec of arc or better.
- 5) Symptomatic PPCS-CI defined as:
  - Near point of convergence (NPC)  $\geq 6\text{cm}$
  - Positive fusional vergence (PFV) at 40cm not meeting Sheard's criteria of at least twice the near phoria or a range of  $\leq 15\Delta$
  - CI symptom survey score (CISS) of  $\geq 21$  for adults and  $\geq 16$  for children
  - Diagnosis of a concussion from a clinician where symptoms persist for 1 to 6 months post injury
- 6) Parental/guardian permission (informed consent) and if appropriate, child assent.

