## **6 STATISTICAL CONSIDERATIONS**

### **6.1 Primary Endpoint**

The primary endpoint will be the change in composite clinical parameters of near point of convergence and positive fusional vergence between the initial assessment and the outcome visits.

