#### **6.3.2 Efficacy Analysis**

The primary analysis will be based on an intention to treat approach and will include all subjects randomized at their initial assessment.

The primary efficacy endpoint will be the change in composite clinical parameters of near point of convergence and positive fusional vergence between the initial assessment and the outcome visits. A repeated measures ANOVA will be used to assess the clinical parameters as well as the chi-squared test using predetermined published optometric benchmarks for improvement.

Secondary endpoints will include the rate of symptom remediation in OBVAT+SCC group compared to SCC alone, change in vision function, and fMRI measures between the start and end of the treatment phase.

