## 9 STUDY ADMINISTRATION

### 9.1 Treatment Assignment Methods

#### 9.1.1 Randomization

A member of the study team will randomize case subjects who consent to participate into one of the treatment groups at the conclusion of their initial assessment. Participants will be randomly allocated by a member of the study team using a pre-determined block randomization procedure. Subjects will be randomized in a 1:1 ratio. Block sizes will be multiples of 4, to reduce the potential size of imbalance across the 2 intervention arms. All participants will be assigned a unique identification number at enrollment, which the study team will use to track subjects' date of enrollment, assigned treatment group, and timeline of their treatment phase.

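### The named efficacy tests make no use of age, although the protocol calls adolescents slower to recover: a small, avoidable loss of precision with no pre-specified protection against chance age imbalance

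*Protocol*

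**What the plan says.** - **Age and recovery.** Section 1.3 states: "Adolescents are particularly vulnerable to the cognitive and developmental concussion consequences, often having a prolonged recovery and poorer outcomes than adults". The sentence is about concussion in general.
- **Population.** Section 3.4.2 admits "Males or females age 11 to 35 years". It also requires a "CI symptom survey score (CISS) of" at least 21 for adults and at least 16 for children, without giving the age that separates the two.
- **Allocation.** Section 9.1.1: "Subjects will be randomized in a 1:1 ratio" and "Block sizes will be multiples of 4, to reduce the potential size of imbalance across the 2 intervention arms". Section 3.2 describes allocation "at the conclusion of their initial assessment using a random number generator". Neither section names a stratification factor, and sections 3.1.2, 5.1.3 and 7.1 name none either.
- **Endpoint and tests.** Section 6.1: "The primary endpoint will be the change in composite clinical parameters of near point of convergence and positive fusional vergence". Section 6.3.2: "A repeated measures ANOVA will be used to assess the clinical parameters as well as the chi-squared test", the latter against published optometric benchmarks. The Synopsis names a Wilcoxon signed test, a paired t-test and Tukey post-hoc comparisons.
- **Use of age.** Section 5.1.1 lists age among the items taken from the record. For the randomised comparison, age then appears only in the descriptive baseline summary of section 6.3.1. Age matching is mentioned only for the healthy controls.

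**The concern.** The protocol itself gives a reason to expect age to matter for recovery, admits a range from early adolescence to the mid-thirties, and then names tests that ignore age. The blocks balance arm totals, not the age mix within them.

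If change over the 6 weeks to outcome visit 1 differs by age, two things follow. The variation due to age stays in the error term and costs some power. And if one arm happens to receive more adolescents, part of the observed arm difference reflects age, with no adjusted analysis fixed in advance. A covariate added after such an imbalance has been seen would look data-driven.

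The repeated measures ANOVA could carry age, but the protocol does not say that it will. A plain chi-squared, Wilcoxon signed or paired t-test cannot carry it at all.

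**Working it through.** **Inputs from the protocol.** Section 6.4 gives 80% power, alpha 0.05 (two-sided assumed), 46 per arm rounded to 50, and 150 subjects finishing. Two arms of 50 make 100, whereas 150 finishing means 75 per arm, so both sizes are shown. The 46 per arm cannot be reproduced because section 6.4 states no effect size; 80% power is taken as the design point.

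**Assumptions, because the protocol is silent.** Adolescent share p = 0.5 (0.3 and 0.7 also tried). Age effect d = 0.5, range 0.3 to 0.8, being the adolescent-adult difference in mean change in units of the within-age-group SD.

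**1. Precision.** With p = 0.5, the share of variance in change due to age is R² = 0.25d²/(1 + 0.25d²). Adjusted power is Φ(2.80/√(1 − R²) − 1.96), where 2.80 = 1.96 + 0.84.

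| d | R² | Power, from 80% |
|---|---|---|
| 0.3 | 0.0225/1.0225 = 2.2% | 80.9% |
| 0.5 | 0.0625/1.0625 = 5.9% | 82.3% |
| 0.8 | 0.16/1.16 = 13.8% | 85.5% |

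In sample-size terms at d = 0.5: 46 × (1 − 0.059) = 43.3, so 44 instead of 46 per arm.

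**2. Chance imbalance in adolescent share.** Exact difference of two independent binomials:

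| Per arm | p | Gap above 10 points | Gap of 20 points or more |
|---|---|---|---|
| 50 | 0.5 | 27% | 5.7% |
| 50 | 0.3 or 0.7 | 23% | 3.8% |
| 75 | 0.5 | 22% | 1.8% |
| 75 | 0.3 or 0.7 | 18% | 1.0% |

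**3. What a gap does to the estimate.** Shift = d × gap.
- 10 points: 0.03, 0.05 and 0.08 SD for d = 0.3, 0.5 and 0.8.
- 20 points: 0.06, 0.10 and 0.16 SD.
- Standard error of the arm difference, √(2/n): 0.20 SD at 50 per arm, 0.16 SD at 75.

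At 50 per arm, even the largest of these shifts (0.16 SD) is below one standard error.

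**4. Type I error.** For a given gap, the unadjusted test has its null distribution shifted by s = d × gap/√(2/n), while its standard error still contains the age variation. The effective critical value is c = 1.96√(1 + 0.25d²), and the conditional error is Φ(−c + s) + Φ(−c − s). At 50 per arm:
- 20-point gap: 5.8%, 7.0% and 9.7% for d = 0.3, 0.5 and 0.8.
- 10-point gap: 5.0% for all three.
- Averaged over all possible allocations: 5.0% for all three.

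The larger age variance in the standard error offsets the shifts on average, so overall error is not inflated.

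**The case against.** **Covariates are ordinary analysis-plan content.** The plan is not shown, and the ANOVA as named does not exclude age. This stands for the ANOVA. It does not stand for the chi-squared, Wilcoxon and paired t-tests, which the protocol has fixed and which cannot take age without being replaced.

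**The premise does not reach the tested endpoint.** Section 1.3 speaks of concussion in general, and no section says that change in NPC or PFV differs by age. Sections 1.1 and 1.3 describe the therapy as effective in both children and adults with typically occurring convergence insufficiency. Section 3.4.2 uses one NPC and one PFV threshold for all ages and admits only patients still symptomatic at 1 to 6 months. This stands: an age effect on the primary endpoint is plausible, not documented, and its size is assumed.

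**The symptom cut-offs.** A reader might infer that the pooled chi-squared test mixes groups judged by different symptom thresholds. The documents do not support this. The 16 and 21 values are eligibility limits, while the chi-squared test in section 6.3.2 concerns the clinical parameters. The cut-offs would come nearer to the primary endpoint only under the Abstract, which calls symptom reduction primary and so conflicts with section 6.1. Nor does the protocol equate the adolescents of section 1.3 with the children of section 3.4.2.

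**Other factors are unstratified too.** Site, time since injury and vestibular involvement are also absent, and age strata across three sites would leave more incomplete blocks. This stands, and is why stratified allocation is only an option here.

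**Conclusion.** The point holds as a minor one. The protocol gives its own reason to expect age to matter for recovery after concussion, records age, and names efficacy tests that do not use it. The cost is modest precision, about 2 power points at an assumed age effect of 0.5 SD and about 1 to 6 over 0.3 to 0.8 SD, plus the absence of a pre-specified adjustment should the arms differ in age mix.

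A reader might infer that the trial is biased or its false-positive rate inflated. It is not. Unstratified blocked 1:1 allocation is valid, and overall type I error is 5%. The conditional rate of about 7% (5.8 to 9.7%) applies only given a 20-point gap at 50 per arm, and a gap of that size or more has a probability of about 6%.

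All sizes rest on an assumed age effect and on half the subjects being adolescents. If age is unrelated to change in NPC and PFV, adjustment gains nothing on the primary endpoint and costs one or two degrees of freedom.

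**What to change.** - **Section 6.3.2, models.** Pre-specify age, in years or as child/adult, as a covariate in the NPC and PFV models. In a repeated measures ANOVA, age has to enter with its interaction with visit (or as a covariate in a model for change). A main effect of age alone would leave the arm-by-visit test unchanged.
- **Section 6.3.2, proportions.** Replace the pooled chi-squared test by a Cochran-Mantel-Haenszel test stratified by child/adult, and use the same test for the symptom remediation rate. State the age that divides the two groups, since section 3.4.2 uses the labels without a boundary.
- **Synopsis.** Align the list of tests with section 6.3.2 as revised.
- **Section 9.1.1, optional.** Stratify the remaining allocation by child/adult. This keeps the age mix close between arms but adds incomplete blocks and list administration. Covariate adjustment gives most of the benefit without it.

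The analysis changes need no new data and no extra subjects. They cost one or two degrees of freedom and some wording, and should be fixed before outcome data are examined by arm.

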## **1.4 Compliance Statement**

This study will be conducted in full accordance all applicable NJIT and Children's Hospital of Philadelphia Research Policies and Procedures and all applicable Federal and state laws and regulations including 45 CFR 46. All episodes of noncompliance will be documented.

The investigators will perform the study in accordance with this protocol, will obtain consent and assent, and will report unanticipated problems involving risks to subjects or others in accordance with The Children's Hospital of Philadelphia IRB Policies and Procedures and all federal requirements. Collection, recording, and reporting of data will be accurate and will ensure the privacy, health, and welfare of research subjects during and after the study.

## **2 STUDY OBJECTIVES**

The purpose of the study is to determine the neurophysiology of and treatment for PPCS-CI.

### **2.1 Primary Objective (or Aim)**

The primary objective of this study is to determine the neural mechanistic differences between PPCS-CI and TYP-CI.

---

## **2.2 Secondary Objectives (or Aim)**

The secondary objectives are to:

- Determine the underlying neural mechanism of OBVAT administered to PPCS-CI patients.
- Compare the effectiveness of standard-community concussion care (SCC) plus 12 vs.16 one-hour OBVAT sessions compared to SCC alone.

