### Study Interventions and Measures:

This study will compare the outcomes of adolescents and young adults with persistent post-concussive symptoms with convergence insufficiency who are randomized to standard-community concussion care (SCC) plus office-based vergence/accommodative therapy (OBVAT) versus those randomized to SCC alone to evaluate the effect of OBVAT in adolescents and young adults with PPCS-CI.

The primary endpoint of this study is the reduction in visual symptoms. This study will also assess the change in vision function measures and fMRI results of those that perform OBVAT compared to those who complete SCC. Additionally, this study will also assess the dose response of 12 OBVAT sessions as compared to 16 sessions.

---

---

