| Study Objective(s)                                                     | 
Primary
 
 
To compare the effectiveness of SCC plus OBVAT compared to SCC only.
 
 
Secondary
 
 
To determine the neural mechanism of OBVAT for PPCS-CI compared to SCC
 
To determine the effectiveness of 12 one-hour sessions compared to 16 one-hour sessions of OBVAT.
 
To compare the differences between PPCS-CI and TYP-CI.
 
                                                                                                                                                                                                                                                   |
| Test Article(s)
(If Applicable)                              | Office-based vergence/accommodative therapy plus standard-community concussion care vs. standard-community concussion care alone.                                                                                                                                                                                                                                                                                                                                                                                                                                                                                                                                                                                          |
| Study Design                                                           | Randomized controlled trial. Phase I                                                                                                                                                                                                                                                                                                                                                                                                                                                                                                                                                                                                                                                                                       |

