| Study Phases
Screening
Study Treatment
Follow-Up | 
Screening and Initial Assessment: All patients who present to the Children’s Hospital of Philadelphia, Somerset Pediatric Group, JFK Institute or Rothman Orthopedic with a concussion date of injury 1-6 months ago will be screened for enrollment as case subjects using the protocol inclusion and exclusion criteria. Clinicians specializing in concussion management will identify potential subjects under their care in clinics after a standard clinical evaluation that consists of a detailed history and examination. A member of the study team will introduce the study to subjects deemed eligible to participate, obtain verbal consent to screening, and screen them against study inclusion and exclusion criteria. Eligible subjects will have time to ask questions and consider participation prior to consenting. Parental/guardian permission (informed consent) and, if applicable, child assent, will be obtained prior to any study related procedures being performed. After consenting to participate, subjects will complete an initial optometric exam, vision assessments, fMRI (NJIT site only), and a patient-reported symptom questionnaire. Data from control subjects recruited from local colleges and universities who did not have a recent concussion have already been collected.
 
Intervention: Case subjects will be randomly assigned into one of two arms. Arm 1 will begin OBVAT immediately, while arm 2 will start with 6 weeks of SCC followed by the OBVAT intervention. A member of the study team will connect subjects with the study vision therapist who will perform their OBVAT sessions. Arm 1 subjects will complete 12 1-hour bi-weekly OBVAT sessions with the vision therapist in addition to SCC while arm 2 subjects complete SCC alone. After 6 weeks, subjects will complete outcome visit 1. After outcome visit 1, arm 1 cases will complete 4 more OBVAT sessions and then complete outcome visit 2. After the initial 6 weeks, arm 2 cases will complete 16 1-hour bi-weekly OBVAT sessions and then complete outcome visit 2. All case subjects will complete at-home reinforcement activities during their OBVAT intervention.
 |

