#### 9.1.2 Blinding

Physicians specializing in concussion will identify subjects and then refer them to trained members of the study team who will handle the consent and randomization processes. Physicians will continue routine clinical care for all subjects. Licensed, practicing optometrists will complete the vision assessments, with a different optometrist completing outcome visit 1 and outcome visit 2 for each participant in order to remain blinded.

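### The 12-versus-16-session comparison, and 16 sessions versus SCC alone, cannot be read as treatment or dose effects, because neither has a randomised, concurrent comparator

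*Protocol*

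**What the plan says.** The dose question appears three times, each time without qualification:

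- Section 2.2 (secondary objectives): "Compare the effectiveness of standard-community concussion care (SCC) plus 12 vs.16 one-hour OBVAT sessions compared to SCC alone".
- Synopsis, secondary objectives: "To determine the effectiveness of 12 one-hour sessions compared to 16 one-hour sessions of OBVAT".
- Abstract, Study Interventions and Measures: "this study will also assess the dose response of 12 OBVAT sessions as compared to 16 sessions".

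The design is set out elsewhere. The synopsis (Study Phases) states: "Arm 1 will begin OBVAT immediately, while arm 2 will start with 6 weeks of SCC followed by the OBVAT intervention". Section 9.1.1 adds: "Subjects will be randomized in a 1:1 ratio". On what follows the first outcome visit in arm 1, the synopsis says: "After outcome visit 1, arm 1 cases will complete 4 more OBVAT sessions and then complete outcome visit 2". Section 4.2 gives arm 2 six weeks of SCC, then Outcome Visit 1, then 16 sessions, then Outcome Visit 2. Section 9.1.2 has the vision assessments done by optometrists, "with a different optometrist completing outcome visit 1 and outcome visit 2 for each participant".

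**The concern.** A dose comparison needs groups that differ in the number of sessions and are otherwise alike, above all in time since baseline. Here the randomised factor is when OBVAT starts, not how much is given. If the objective is taken at its word, any improvement between the two outcome visits could be credited to the four extra sessions when it comes from continuing recovery or from repeating the tests. The subjects are one to six months past a concussion, so recovery over time is plausible. Section 1.3 itself cites a fall in persistent symptoms from 46% at two weeks to 33% at four weeks. That interval is earlier than this trial's window and gives no rate for it. At stake is a conclusion about the length of a course of therapy that the design cannot support.

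**Working it through.** **1. Sessions and time at each visit.** Inputs: section 4.2 (sessions before each visit) and section 3.3.1 (Phase 1 of 6 ± 2 weeks; Phase 2 of 2 ± 1 weeks in arm 1 and 8 ± 2 weeks in arm 2). I read bi-weekly as twice a week, because 12 sessions then fit into 12 / 2 = 6 weeks. Weeks are counted from the start of Phase 1.

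| | Outcome Visit 1 | Outcome Visit 2 |
|---|---|---|
| Arm 1 | 12 sessions, week 6 | 16 sessions, week 6 + 4/2 = 8 |
| Arm 2 | 0 sessions, week 6 | 16 sessions, week 6 + 16/2 = 14 |

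Arm 2 is never assessed at 12 sessions.

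**2. Contrasts that the table allows.**

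- *12 + SCC versus SCC alone:* arm 1 versus arm 2 at Outcome Visit 1. Randomised and concurrent.
- *12 versus 16, within arm 1:* Outcome Visit 2 minus Outcome Visit 1. Uncontrolled before-after change over about two weeks, with a different optometrist.
- *12 versus 16, between arms:* arm 2 at Outcome Visit 2 versus arm 1 at Outcome Visit 1. The difference in time is 14 − 6 = 8 weeks, and arm 2 has had six weeks of SCC first.
- *16 versus SCC alone:* arm 1 at week 8 versus arm 2 at week 6 is not concurrent. Arm 2 at Outcome Visit 2 versus its own Outcome Visit 1 is an uncontrolled before-after change. After Outcome Visit 1 nobody is on SCC alone.

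Only the first contrast isolates a treatment effect.

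**3. What time alone could add.** The protocol gives no recovery rate. If symptoms fell by an assumed 0.25 to 1.0 CISS points per week, the within-arm contrast would carry 2 × 0.25 = 0.5 to 2 × 1.0 = 2 points unrelated to dose. The between-arm contrast would carry 8 × 0.25 = 2 to 8 × 1.0 = 8 points.

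**4. How often drift would look like a dose effect.** This is an illustration only. Let δ be the mean change between the outcome visits in arm 1 that is unrelated to the extra sessions, in SDs of the within-subject change between those visits. A two-sided paired t-test at 0.05 has noncentrality δ√n on n − 1 degrees of freedom. Section 6.4 gives 50 per arm. The target of 150 evaluable subjects at 1:1 gives 150 / 2 = 75.

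| δ (assumed) | n = 50: δ√n | Probability significant | n = 75: δ√n | Probability significant |
|---|---|---|---|---|
| 0.1 | 0.71 | 11% | 0.87 | 14% |
| 0.2 | 1.41 | 28% | 1.73 | 40% |
| 0.3 | 2.12 | 55% | 2.60 | 73% |

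A larger sample makes a wrong dose conclusion more likely, not less.

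**5. The protocol's own sample size.** Section 6.4 (46 per arm, rounded to 50) concerns OBVAT versus placebo in TYP-CI. It states no expected difference between 12 and 16 sessions, so there is no figure on this question to reproduce.

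**The case against.** The best defence is that this is a secondary objective. The protocol nowhere says that the dose comparison is randomised or confirmatory, and section 6 gives it no test of its own. A within-arm look at further change is an ordinary exploratory question, and its analysis may be set out in a SAP that is not shown. This stands in part. The arm 1 change can be estimated and reported. But no analysis plan can supply a missing 12-session comparison group or a late SCC-only group, and the objective as worded promises effectiveness and dose response.

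It can also be said that arm 2's change from baseline to Outcome Visit 1 under SCC alone gives some measure of recovery and retest effects. It does, and it could serve as a benchmark. It covers an earlier and longer period (six weeks, not two), in subjects not yet treated, so it is not a concurrent control.

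Three stronger readings are tempting and are not supported:

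- *The whole section 2.2 objective fails.* It does not. SCC plus 12 sessions versus SCC alone at Outcome Visit 1 is sound in design.
- *The change of optometrist biases the comparison.* Section 9.1.2 makes the change certain within each participant. It does not say that one set of optometrists does all first visits and another all second visits. If they rotate, the effect is noise. Bias in NPC and PFV is possible but not shown, and the self-reported surveys are less exposed.
- *The sponsor will report the change as a dose effect.* No text says so. The wording permits it.

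**Conclusion.** The concern holds for two parts of the objective: 12 versus 16 sessions, and 16 sessions versus SCC alone. Neither can be answered as a treatment or dose effect, because the number of sessions is tied to visit and time, and the SCC-only period ends at Outcome Visit 1. This follows from sections 4.2 and 9.1.1 and needs no numerical assumption beyond reading bi-weekly as twice weekly for the approximate weeks.

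The size of the possible error is not known. The probabilities of 11% to 55% (n = 50) and 14% to 73% (n = 75) rest on assumed drifts of 0.1 to 0.3 SD of the within-subject change, for which the protocol gives no basis. With little drift they approach the nominal 5%. They also assume that all 50 or 75 subjects in arm 1 provide both visits; the 50 in section 6.4 is a figure already inflated for losses.

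Other rules narrow what the arm 1 change can show. Outcome visits wait for completion of the sessions (section 7.1.1), and longitudinal data of subjects who withdraw are excluded (section 4.3.1), so it describes completers. Arm 1 has no fMRI at Outcome Visit 2 (sections 4.2.8 and 5.2.1), so imaging cannot address 12 versus 16 within that arm.

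**What to change.** Change the wording in section 2.2, in the abstract (Study Interventions and Measures) and in the synopsis objective:

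1. Limit the comparison with SCC alone to SCC plus 12 sessions versus SCC at Outcome Visit 1.
2. Drop the terms dose response and effectiveness of 12 compared with 16. Put in their place: *exploratory, non-randomised, uncontrolled description of the further change from Outcome Visit 1 (12 sessions) to Outcome Visit 2 (16 sessions) within arm 1, with estimate and 95% CI*.
3. Add: *this change will not be interpreted as the causal effect of the four additional sessions*.

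The session schedule, visits and sample size stay as they are. The cost is a wording amendment, and the sponsor gives up a dose claim that the design cannot support.
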